### Trial design

A single-center, double-blind, randomized, parallel, prospective clinical trial will be conducted at the Sharad Pawar Dental College, Datta Meghe Institute of Higher Education and Research (DMIHER), Sawangi, Wardha.

Two groups will be created:

Group A – Diclofenac sodium

Group B – Aescin (escin)

The randomization process will be performed using a computer-generated subject allocation list.

Trial participants and outcome assessors will be blinded. The study will be a double-blinded clinical trial where the participant and the principal investigator will not be aware of the drug being used in the postoperative period. The double-blinded study minimizes the risk of various types of biases, such as observer bias or confirmation bias, which may influence the results of the investigation.

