### Participant timeline

Pain, facial swelling, mouth opening, serum C-reactive protein, and salivary prostaglandin E2 levels will be recorded preoperatively (T0) on the second postoperative day (T1) and fifth postoperative day (T2).

Patient satisfaction regarding therapy and the need for rescue analgesics will be recorded on the fifth postoperative day.

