### Sample size

The study will be a non-inferiority trial with a continuous outcome.

The sample size was established based on data obtained from a previous study conducted by Salgia et al.
^
11
^ Serum C-reactive protein level was chosen as the primary outcome variable.

Formula using mean difference

$$n1=n2=2\frac{{\left(Z_{\alpha }+Z_{\beta }\right)}^{2}\sigma^{2}}{{\left(\delta \right)}^{2}}$$

$$Z_{\alpha }=1.96\;$$

α = Type I error at 5% at both sides two tailed

Z
_β_ = 0.84 = Power at 80%

Primary Variable = CRP (C-reactive protein) levels

The mean difference after treatment CRP (mean ± SD) for the diclofenac group was 16.305 ± 3.977 (as per the reference article).
^
10
^

Considering 20% clinically relevant margin for aescin = (

16.305∗20)/100=3.26

Sample size:

$$N=n1=n2=2\frac{{\left(1.96+0.84\right)}^{2}{\left(3.977\right)}^{2}}{{\left(3.261\right)}^{2}}=23$$

Assuming 10% dropout = 2

Total sample size required = 23 + 2 = 25 each group.

Thus, a total sample size of 50 subjects presenting with impacted mandibular third molars will be enrolled in the study.

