### Statistical analysis plan

**
*Statistics: outcomes*
**

**
*Statistics: additional analyses*
**

**
*Statistics: analysis population and missing data*
**

*Primary variable*

Inferential statistics will be used to compare the two groups for measurement scores, resulting in their mean change in a primary variable (visual analog scale, facial swelling, mouth opening, salivary prostaglandin E2, serum C-reactive protein) between baseline and end visits.

Baseline variables will be tested for significance in the mean using ANOVA or Kruskal-Wallis test for more than two assessment periods. A post-hoc (Tukey’s or Duncan’s) test will be used to find a significant difference between the two groups for pair-wise comparison.

*Outcome variables*

Outcome variables will be tested for intra-difference in measurement at pre- and post-visits using a paired t-test to determine the mean’s significance. The unpaired t-test for comparison of two groups and ANOVA for comparison of three groups will be used for intergroup differences.

Statistical analysis will be carried out using R-software free version.

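### Across-visit tests are for independent samples although the same patients are measured at T0, T1 and T2, and the post-hoc and three-group tests have no use in a two-arm trial

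*Protocol article*

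**What the plan says.** Three places in the protocol article matter.

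- **Trial design.** "Two groups will be created": diclofenac sodium and aescin.
- **Participant timeline.** Pain, swelling, mouth opening, serum CRP and salivary PGE2 "will be recorded preoperatively (T0) on the second postoperative day (T1) and fifth postoperative day (T2"). Each patient therefore contributes three linked values per outcome.
- **Statistical analysis plan.** The section first says that the two groups will be compared on mean change between baseline and end visits. It then gives the across-visit rule: "Baseline variables will be tested for significance in the mean using ANOVA or Kruskal-Wallis test for more than two assessment periods". A Tukey or Duncan post-hoc "test will be used to find a significant difference between the two groups for pair-wise comparison". Under outcome variables it adds: "Outcome variables will be tested for intra-difference in measurement at pre- and post-visits using a paired t-test", and finally: "The unpaired t-test for comparison of two groups and ANOVA for comparison of three groups will be used for intergroup differences".

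The section names no repeated-measures ANOVA, Friedman test or mixed model.

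**The concern.** Three of the named procedures do not match the design.

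1. **Visit comparison.** Kruskal-Wallis and one-way ANOVA assume independent samples. Here the visits are repeated measurements on the same patients. These tests leave the stable differences between patients in the error term, so their p-values for change over time are wrong.
2. **Post-hoc test between two groups.** Two arms form a single pair, so a multiple-comparison step has nothing to add.
3. **Three-group ANOVA.** There is no third group.

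The across-visit sentence is also garbled. It speaks of baseline variables, which are measured once, and of more than two assessment periods. If it means a comparison of arms at baseline, it tests only chance in a randomised trial. If it means a comparison of visits, the first problem applies.

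What is at stake is the time course of the five repeated outcomes. A real change between visits could be missed, or the analyst could have to choose a substitute test after seeing the data.

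**Working it through.** **Inputs.** Two arms (Trial design). Three visits per patient (Participant timeline). Number of patients per arm from Sample size: 2 × (1.96 + 0.84)² × 3.977² / 3.261² = 2 × 7.84 × 15.816 / 10.634 = 23.32. The plan states 23, or 25 with dropout, so its figure reproduces apart from rounding down. The within-patient correlation ρ is not given; 0.3 to 0.7 is assumed, equal for every pair of visits, with normal data and equal variances.

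**Step 1: why the one-way test is off.** With n patients in one arm and unit variance:
- the between-visit sum of squares with no true change is distributed as (1 − ρ)·χ² on 2 df;
- the one-way error sum of squares is (1 − ρ)·χ² on 2(n − 1) df plus (1 + 2ρ)·χ² on n − 1 df.

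The expected one-way error mean square is [2(1 − ρ) + (1 + 2ρ)]/3 = 1, whereas the correct error variance for visit comparisons is 1 − ρ. At ρ = 0.5 the F ratio is therefore about half what it should be. A repeated-measures ANOVA removes the patient term and uses 1 − ρ.

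**Step 2: actual type I error at a nominal 5%, n = 23 to 25 (simulation).**

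| ρ | One-way ANOVA | Kruskal-Wallis (n = 25) | Repeated-measures ANOVA |
|---|---|---|---|
| 0 | 5.0% | 5.6% | 5% |
| 0.3 | 1.6–1.7% | 1.9% | 5% |
| 0.5 | 0.3–0.4% | 0.4% | 5% |
| 0.7 | 0.02–0.04% | 0.1% | 5% |

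The ranges cover runs of 20,000 and of 4 million simulated arms. Kruskal-Wallis used 4,000. Friedman, the rank-based test for repeated measures, stayed at 5.5–5.7% in the same 4,000-run simulations.

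**Step 3: power at ρ = 0.5, n = 23.** The shifts at T0, T1 and T2 are assumptions.

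| Shifts (SD) | One-way ANOVA | Repeated-measures ANOVA |
|---|---|---|
| 0, 0.4, 0.2 | about 0.10 | about 0.37 |
| 0, 0.6, 0.3 | 0.33 | 0.70 |
| 0, 1.0, 0.5 | 0.90 | 0.99 |
| 0, 1.5, 0.75 | about 1.00 | about 1.00 |

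**Step 4: post-hoc test with two groups.** On one simulated data set with 25 per arm, Tukey, the unpaired t-test and ANOVA all gave p = 0.2771. They are the same test when there is one pair.

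**Step 5: gain from adjusting for T0.** With equal variances, the arm difference in change scores has variance proportional to 2(1 − ρ). Adjusted for the T0 value it is proportional to 1 − ρ². The ratio is (1 − ρ²)/[2(1 − ρ)] = (1 + ρ)/2, that is 0.65, 0.75 and 0.85 at ρ = 0.3, 0.5 and 0.7.

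**The case against.** **ANOVA is unqualified and could mean repeated-measures ANOVA in a condensed article.** This is possible. However, the alternative named beside it is Kruskal-Wallis, an independent-samples test, and the follow-up tests are said to compare the two groups. The wording points to the one-way test, and for Kruskal-Wallis there is no such doubt.

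**Details may be left to an unseen analysis plan.** That would answer an omission. Here the tests are written down, and some cannot be applied to the design.

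**The power loss rests on assumed shifts.** This stands. The only effect figure in the article is the CRP mean difference of 16.305 with SD 3.977. If that is a change over time, it is 16.305/3.977 = 4.1 SD, and either test would detect it. The loss matters for outcomes or visit pairs with modest changes.

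**The section also names tests that fit.** This stands too. The paired t-test respects the pairing, and the unpaired t-test on change from T0 to T2 is a valid comparison of the arms.

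A reader might go further in three ways that the documents do not support:
- *That no valid arm comparison is planned.* The change-score t-test gives one for the end visit.
- *That false-positive arm differences will be inflated because visits are pooled as independent.* Nothing in the article says that visits will be pooled to compare arms, and the across-visit error runs in the conservative direction.
- *That Duncan's test inflates the family-wise error.* It is only an alternative to Tukey, and two arms offer no multiplicity. Applied across the three visits with the one-way error term (n = 23), its simulated family-wise error is about 3.8–3.9%, 1.3% and 0.1% at correlations 0.3, 0.5 and 0.7, below 5% in each case.

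**Conclusion.** The concern holds in a limited form. The across-visit test as worded treats repeated measurements as independent, the two-group post-hoc step is redundant, and the three-group ANOVA has no object. The first error is conservative: actual type I error falls from 5% to about 1.6–1.7% at correlation 0.3 and to about 0.02–0.04% at 0.7. The power cost ranges from large (about 0.10 against 0.37) to negligible, depending on how far the visits really differ. These sizes rest on an assumed correlation, compound symmetry and illustrative shifts.

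The main arm comparison, change from T0 to T2 by unpaired t-test, is not invalidated. The section names that contrast but no comparison of the arms at T1, although all five outcomes are measured then. This should be corrected before analysis, but it does not threaten the trial's central comparison.

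**What to change.** In the statistical analysis plan section:

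1. Delete the three-group ANOVA, the Tukey/Duncan step between the two groups, and the significance test of baseline variables. Describe baseline by arm instead.
2. For comparisons across T0, T1 and T2, replace ANOVA or Kruskal-Wallis with a repeated-measures method: a mixed model, or repeated-measures ANOVA with Friedman as the rank-based alternative.
3. Estimate the arm difference at T1 and at T2, with 95% confidence intervals, from a model adjusted for the T0 value. Either a mixed model on T1 and T2 with arm, visit and arm-by-visit terms, or an ANCOVA at each visit, would do.

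The mixed model is not the only valid choice; what matters is that one method is fixed in advance. The change does not settle which visit is primary or how the non-inferiority margin is tested, and those need their own wording.

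The cost is a few sentences and slightly more analysis work in R, which the plan already names. No extra data or patients are needed. The variance of the arm difference falls to 65–85% of that of the change score at correlations 0.3 to 0.7.

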Graziani et al. (2017) enrolled 40 patients in a case-control study demonstrating systemic inflammation following third molar removal. Patients who underwent third molar removal had more significant systemic inflammation, oxidative stress, and triglyceride levels than controls, and the first postoperative week had increased WBC counts and serum C-reactive protein and fibrinogen levels. The baseline values of the markers were observed three months after extraction. Higher systemic inflammation is associated with impacted third molars, and their elimination may signify a novel method for investigating acute inflammation and defining favorable systemic outcomes in humans.
^
8
^

Mehra et al. (2013) conducted a double-blind, randomized clinical trial of 80 patients to assess the effect of four different pharmacological regimens on prostaglandin E2 (PGE2) levels in urine and saliva. Saliva and urine samples were collected at planned intervals. After removing the impacted lower third molars, the findings were compared with clinical progression. Patients who received ibuprofen fared significantly better in terms of most parameters. They further concluded that PGE2 is measurable in saliva and urine, and its rise and fall can be detected in both saliva and urine. They further suggested that PGE2 correlates with subjective and objective clinical symptomatology and that administration of anti-inflammatory drugs manipulates its levels in the body.
^
5
^

The current scientific literature must be more extensive in demonstrating the correlation of the drug’s efficacy with reliable inflammation markers and associated clinical symptomatology.

Considering this, the present study will be a randomized, double-blind, non-inferiority trial to compare the efficacy of aescin and diclofenac sodium in the management of postoperative pain, swelling, and mouth opening, as well as their effects on salivary Prostaglandin E2 and serum C-reactive protein levels after surgical removal of the impacted mandibular third molar. The trial will be conducted as per SPIRIT guidelines.
^
15
^

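### Declared and sized as a non-inferiority trial on a CRP margin of 3.26, but every planned between-group test is a test for a difference and the margin is never used in the analysis

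*Protocol article*

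**What the plan says.** The Sample size section of the protocol article states: "The study will be a non-inferiority trial with a continuous outcome". It adds: "Serum C-reactive protein level was chosen as the primary outcome variable". The inputs are a diclofenac CRP figure ("for the diclofenac group was 16.305 ± 3.977"), a margin introduced as "Considering 20% clinically relevant margin for aescin" and worked out as 3.26, an error rate described as "Type I error at 5% at both sides two tailed" with Z = 1.96, and 80% power. These give 23 per group, raised to 25 for dropout. The Discussion restates the framework: "the present study will be a randomized, double-blind, non-inferiority trial to compare the efficacy of aescin and diclofenac sodium".

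The section headed Statistical analysis plan then names the tests. Between groups: "The unpaired t-test for comparison of two groups and ANOVA for comparison of three groups will be used for intergroup differences". It also names ANOVA or Kruskal-Wallis, followed by a Tukey or Duncan post-hoc test meant to detect a significant difference between the two groups. It gives no non-inferiority hypothesis, no confidence interval set against a margin and no decision rule. The figure 3.26 appears only in the Sample size section. The analysis section also lists five measures (VAS, swelling, mouth opening, PGE2 and CRP) under its primary variable heading, and compares their mean change from baseline to the end visit.

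**The concern.** A non-inferiority claim requires rejecting the hypothesis that aescin is worse than diclofenac by the margin or more. The unpaired t-test has a different null hypothesis, that the two means are equal. Failing to reject equality says nothing about whether a deficit of 3.26 has been excluded, so the analysis section does not answer the question for which the trial was sized.

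The Abstract and the Discussion expect aescin to prove clinically acceptable beside diclofenac and possibly an efficacious alternative to NSAIDs. With no rule fixed in advance, such a claim would rest either on a non-significant p-value, which has no error control at the margin, or on a criterion chosen after the data are seen.

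**Working it through.** **Inputs, all from the Sample size section.** SD 3.977; margin 0.20 × 16.305 = 3.261; Z values 1.96 and 0.84; 23 evaluable per group, 25 enrolled per group.

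**1. Reproducing the plan's figure.** n = 2 × (1.96 + 0.84)² × 3.977² / 3.261² = 23.32 per group, which the article gives as 23; rounding up gives 24. The same formula serves a two-sided difference test with a true difference of 3.261 and a non-inferiority test at one-sided 2.5% with a true difference of 0. Only the declared framework and the use of 3.26 as a margin make this a non-inferiority sizing. One-sided 5% would give 19, which does not match.

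**2. Precision.** The standard error is 3.977 × √(2/n), and the 95% CI half-width is the t quantile times that.

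| | 23 per group | 25 per group |
|---|---|---|
| Standard error | 1.173 | 1.125 |
| 95% CI half-width | 2.36 | 2.26 |
| t-test non-significant if the observed difference is smaller in size than | 2.36 | 2.26 |
| Non-inferiority met if the observed aescin deficit is below (3.261 minus half-width) | 0.90 | 1.00 |

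At the planned SD, an observed deficit between about 0.9 and 2.4 (23 per group), or 1.0 and 2.3 (25 per group), gives p>0.05 and yet does not exclude the margin.

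**3. How often the two rules disagree.** The t-test figures at the margin and at half the margin are from the noncentral t distribution, as is the margin rule's power at a true difference of 0. At a true difference of 0, the 95% is the complement of the 5% test level. The margin rule's figure at the full margin is its nominal level; its figures at half the margin are from simulation (100,000 trials per setting). Each cell gives 23 per group / 25 per group.

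| True aescin deficit | t-test non-significant | 95% CI excludes the margin |
|---|---|---|
| 0 | 95% / 95% | 77.6% / 81.1% |
| 1.63 (half the margin) | 72.5% / 70.5% | about 27% / 29% |
| 3.261 (full margin) | 22.4% / 18.9% | 2.5% / 2.5% |

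If p>0.05 were taken as showing that aescin is no worse, the false-acceptance rate at the margin would be 22.4/2.5 = 9.0 or 18.9/2.5 = 7.6 times nominal, so roughly 8 to 9 times.

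**4. What the planned test can show.** A significant result in favour of aescin would put the whole interval on the favourable side of zero, which implies non-inferiority. At the true difference of 0 that the sizing assumes, this happens in only 2.5% of trials (half of the 5% significant results), whereas the margin rule succeeds in about 78% to 81%.

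**The case against.** **The full analysis plan may hold the rule.** The article is condensed, and a rule comparing the confidence interval with the margin is often placed in a separate document. Silence would be no finding. But the article is not silent: under a heading for the statistical analysis plan it commits to specific tests, and those do not address the declared hypothesis.

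**The label may be the error, not the tests.** The Abstract, aim, objectives and trial design speak of comparing the drugs and do not mention non-inferiority, and the sizing formula with a two-tailed error rate is also that of a difference trial. This stands. The article does not show which side the sponsor intends, so the fix must allow for both.

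**Three stronger readings that a reader might infer are not supported.**
- That the trial cannot reach a non-inferiority conclusion at all. It can if aescin is significantly better, and the t-test's own data yield an interval that could be set against 3.26. The article simply plans no such step.
- That the sponsor intends to read p>0.05 as comparability. No section says so. The 22% and 19% measure what that reading would cost, not a planned rule.
- That aescin could be significantly worse and still non-inferior. That needs a half-width below 3.261/2 = 1.63 against 2.36 expected, so an observed SD below about 3.977 × 1.63/2.36 = 2.75. The probability is about 0.1%, so it is not a practical possibility at this sample size.

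**Conclusion.** The point holds as an internal contradiction: the framework and margin in the Sample size and Discussion sections do not match the tests fixed in the Statistical analysis plan section. As written, the between-group analysis can support non-inferiority only through a significant advantage for aescin, which is unlikely in the scenario the sizing assumes. A non-significant result would occur in about 22% of trials (23 per group) or 19% (25 per group) with aescin worse by the full margin, against 2.5% under a margin rule.

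These figures assume normally distributed CRP data with SD 3.977 in both groups, equal group sizes, and the margin of 3.261 taken as given. They apply in either direction of scoring, provided that the SD and the margin refer to the variable analysed. The article leaves this unclear: the wording around 16.305 could mean a post-treatment level or a change, while the analysis section compares mean change.

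**What to change.** In the Statistical analysis plan section:

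1. Name serum CRP as the single primary outcome, in line with the Sample size section, and treat the other listed measures as secondary.
2. State the primary CRP variable (post-treatment level or change from baseline), the visit (second or fifth postoperative day) and which direction is worse, consistent with the quantity behind 16.305 and the 3.26 margin.
3. Then add a rule such as: non-inferiority is concluded if the two-sided 95% CI for the difference in mean CRP variable, aescin minus diclofenac, excludes a disadvantage of 3.26 or more. That means an upper limit below +3.26 if higher values are worse, or a lower limit above -3.26 if the variable is a reduction. A non-significant difference will not be read as non-inferiority.

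If the sponsor instead intends a difference trial, remove the non-inferiority label from the Sample size and Discussion sections and make no non-inferiority claim.

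The cost is wording plus the decisions in steps 1 and 2, and the approvals that the article requires for protocol amendments. No extra data are needed, and the planned 50 patients need no material change: exact power under the margin rule at a true difference of 0 is 77.6% with 23 per group and 81.1% with 25. The article reports the study at the pilot stage, so the change can still be made before the main data are analysed.

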### Eligibility criteria

*Inclusion criteria*
1.Patients giving informed written consent.2.Age group 18-40 yrs. The age range is selected to have homogeneity, reduced comorbidities, relevance to the target population and better baseline functionality.3.ASA I and healthy ASA II physical status.4.Patients presenting with impacted mandibular third molars that are indicated for removal.5.Slightly or moderately difficult impacted mandibular third molars, according to the Pederson difficulty index with the difficulty score in the range of 3 to 7.

*Exclusion criteria*
1.Presence of oral mucosal comorbid conditions that may affect salivary inflammatory markers.2.Patients not reporting for follow-up as per study protocol.3.Presence of systemic infections that may alter the levels of serum C-reactive protein.4.Presence of acute infection that necessitates the use of antibiotic therapy.5.Known allergies to drugs under study and local anesthetic agents.6.Patients with a history of xerostomia or hypersalivation.

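### The arms are compared by an unpaired t-test with no baseline covariate, although T0 is recorded; ANCOVA on T0 is a nearly free improvement whose size the protocol does not let us fix

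*Protocol article*

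**What the plan says.** All places are in the protocol article.

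- **Statistical analysis plan, Primary variable.** For five outcomes, serum CRP among them, the groups are compared on mean change "between baseline and end visits".
- **Statistical analysis plan, Outcome variables.** The between-arm method is named: "The unpaired t-test for comparison of two groups". Neither place mentions a covariate or any other baseline adjustment.
- **Sample size.** "Serum C-reactive protein level was chosen as the primary outcome variable". The planning values are given as "The mean difference after treatment CRP (mean ± SD) for the diclofenac group was 16.305 ± 3.977", and the margin is 20% of that mean, 3.26.
- **Participant timeline.** "Pain, facial swelling, mouth opening, serum C-reactive protein, and salivary prostaglandin E2 levels will be recorded preoperatively (T0"), and again on postoperative days 2 (T1) and 5 (T2). The baseline value is therefore planned for every patient.
- **Allocation: sequence generation.** There is no stratification.
- **Eligibility criteria.** Each patient is graded on the "Pederson difficulty index with the difficulty score in the range of 3 to 7".

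The mean change and the t-test stand in separate sentences. Reading them together as a t-test on change from baseline is an inference, though the natural one. If the test is meant for T2 values, T0 is not used at all.

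**The concern.** A change score subtracts the whole baseline value, which amounts to assuming that T2 regresses on T0 with slope 1. A t-test on T2 alone assumes slope 0. Both are unbiased over repeated randomisations. In one trial of 25 per arm without stratification, however, a chance difference in T0 is over- or under-corrected unless the assumed slope happens to be right. ANCOVA estimates the slope from the data.

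The width of the interval matters more than usual here. The trial is described as a non-inferiority trial, so the conclusion depends on where the confidence limit falls against 3.26. The sample size has no slack either: the formula gives slightly more than the 23 per arm that was adopted. Any precision already available in planned data is worth having.

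**Working it through.** **1. The plan's own figure.** Inputs from the Sample size section: Z values 1.96 and 0.84, SD 3.977, margin 0.20 × 16.305 = 3.261.

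n per arm = 2 × (1.96 + 0.84)^2 × 3.977^2 / 3.261^2 = 23.32. The protocol takes 23, adds 2 for dropout, and enrols 25 per arm. This is a two-sample formula with no baseline adjustment.

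**2. Variances of the two estimators.** Let SD2 be the SD of CRP at T2, k = SD(T0)/SD(T2), and rho the within-arm T0-T2 correlation.

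- Change score: SD2^2 × (1 + k^2 - 2 rho k)
- ANCOVA on T0: SD2^2 × (1 - rho^2)
- Ratio, ANCOVA to change: (1 - rho^2)/(1 + k^2 - 2 rho k)
- Ratio, ANCOVA to a t-test on T2 only: 1 - rho^2

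The first ratio never exceeds 1, because the denominator minus the numerator is (k - rho)^2. It equals 1 when rho = k, that is, when the true slope rho/k is 1. If k = 1 it reduces to (1 + rho)/2.

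**3. Values.** The documents give neither rho nor k, so both are assumptions and are shown over a range.

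| k | rho 0.3 | rho 0.5 | rho 0.7 |
|---|---|---|---|
| 1 | 0.65 | 0.75 | 0.85 |
| 0.5 | 0.96 | 1.00 | 0.93 |
| 0.3 | 1.00 | 0.95 | 0.76 |
| 0.2 | 0.99 | 0.89 | 0.67 |

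Example, k = 0.5 and rho = 0.3: (1 - 0.09)/(1 + 0.25 - 0.30) = 0.91/0.95 = 0.96.

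**4. Interval half-width, 25 per arm, taking 3.977 as the SD of change.** Change-score t-test: t(48 df) × 3.977 × sqrt(2/25) = 2.26. For ANCOVA, use 47 df, multiply the variance by the ratio above, and allow for estimating the slope with the factor 1 + 1/(50 - 4).

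- k = 1: 1.84, 1.98 and 2.11 at rho 0.3, 0.5 and 0.7, which is 18%, 12% and 7% narrower.
- k = 0.5, rho 0.3: 2.24, about 1% narrower.
- k = 0.2, rho 0.3: 2.27 to 2.28, slightly less than 1% wider.
- Worst case, rho = k: 2.29, about 1% wider.

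**5. Power at rho 0.3.** Noncentral t, one-sided 2.5%, margin 3.261, 22 and 23 evaluable patients (45 of 50, i.e. 10% lost), one degree of freedom charged to ANCOVA. Because the Sample size wording leaves open whether 3.977 is the SD of a change or of a post-treatment level, both readings are shown.

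| k | 3.977 as SD of change: t-test, ANCOVA | 3.977 as SD of T2 level: t-test on change, ANCOVA |
|---|---|---|
| 1 | 76.7%, 91.5% | 62.2%, 80.4% |
| 0.5 | 76.7%, 78.4% | 78.7%, 80.4% |
| 0.3 | 76.7%, 76.6% | 80.4%, 80.4% |
| 0.2 | 76.7%, 77.1% | 80.0%, 80.4% |

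**6. If 3.977 is a T2-level SD.** The SD of change exceeds it when 1 + k^2 - 2 rho k > 1, that is, when rho < k/2. The threshold is 0.5 if k = 1 and 0.1 if k = 0.2.

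**The case against.** The strongest reply is that nothing here is an error. The unpaired t-test is unbiased and valid under randomisation, it matches the two-sample formula used for sizing, and the absence of stratification does not bias it. That stands: this is a matter of efficiency, not validity.

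The second reply concerns size. A reader might infer from the usual (1 + rho)/2 rule that weak T0-T2 correlation is where change scores lose most, and that ANCOVA would add 15 to 18 points of power at rho 0.3. The documents do not support that. The rule needs equal SDs at T0 and T2, which the protocol nowhere states. The eligibility criteria (ASA I or healthy ASA II, no systemic infection that may alter CRP) make it plausible that CRP varies less before surgery than after, so that k is below 1. Change is then close to the T2 value itself, and weak correlation costs the change score little: between nothing and two points of power at rho 0.3 for k from 0.2 to 0.5. A large gain at small k needs a strong correlation, such as the ratio 0.67 at k = 0.2 and rho 0.7. This reply also stands, and it removes any firm claim about magnitude.

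Third, applying the t-test to change is an inference from two sentences. If the test is applied to T2 values, the change-score figures fall away, but T0 is then ignored altogether and the ratio is 1 - rho^2. The recommendation is the same under either reading.

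**Conclusion.** The point holds as a free improvement. The protocol fixes a between-arm test that leaves planned baseline data out of the model. ANCOVA on T0 is asymptotically at least as precise as either reading of that test, and in a trial of this size it can widen the interval by only about 1%. The gain ranges from essentially nil to an 18% narrower interval over the values of rho and k examined for the half-width. Which end applies cannot be settled from the documents, and the figures rest on assumed rho and k and on one or other reading of the SD of 3.977.

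It should not be read as a finding that the planned analysis is invalid or biased, or that the trial loses a known amount of power by it. Since rho and k are unknown before the data, the sensible choice is the method that cannot materially lose.

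**What to change.** In the Statistical analysis plan section, state that the primary estimate is the aescin-minus-diclofenac difference in T2 CRP from an ANCOVA with arm and T0 CRP, and that its 95% confidence interval is judged against the 3.26 margin. The margin carries over in the same units, because under randomisation the adjusted T2 difference and the difference in T2-minus-T0 change estimate the same quantity. The Pederson score, already recorded for eligibility, may be added as a second covariate; no gain has been calculated for it.

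Use the same model, with each outcome's own T0 value, for VAS pain, facial swelling, mouth opening and salivary PGE2. Specify it before unblinding.

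Cost: one line of wording and one degree of freedom for T0, with one more if the Pederson score is included. No extra patients, visits or measurements are needed.
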